Progressive changes in muscle length and stiffening of joints in the upper limbs can ultimately result in a limited ability to reach, grasp and manipulate objects or, in some individuals, a complete lack of functional use of the hands. Strong correlations exist between the degree of upper limb deformity and activity performance [9]. When combined with neurological dysfunction, upper-limb musculoskeletal impairments significantly impact on the ability of children to use their hands to perform daily activities, attain age appropriate independence and develop the autonomy and skills required to participate in activities of importance in home, school and community environments [10, 11].

Children with CP are not born with musculoskeletal impairments. There is evidence however, that in children with spastic motor types, these impairments begin to manifest prior to three years of age [12] and that increasing stiffness and progressive loss of range of movement occurs throughout childhood and adolescence [13–15].

A range of treatment options are available for children with CP that specifically focus on improving hand use. These include activity-based interventions such as goal-directed training, intensive bimanual therapy, modified constraint-induced movement therapy and home programs. Each of these interventions aim to achieve child/parent-focused goals, and has high-level evidence supporting their effectiveness for increasing activity-level performance and goal achievement [16]. Little evidence is available however, about whether activity-level interventions improve range of movement and reduce secondary musculoskeletal impairments. In addition to activity-based therapies, injection of Botulinum toxin A (BoNT-A) into overactive muscle groups is known to reduce muscle overactivity and has been associated with improved range of movement during a period of chemical denervation, therefore enhancing the effects of upper extremity therapy and the potential for goal achievement and activity performance [17]. Nevertheless, BoNT-A alone in the upper limbs has been shown to have little sustained effect on range of movement [17]. Upper limb surgery is also available to correct deformity once present, although outcomes are variable [18].

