### Sample size

Sample size calculations were performed according to the primary dependent variable: passive range of movement of wrist extension (measured with fingers extended) at 3 years. Sample size calculations were based on data provided by Rameckers et al. [26] who reported a baseline standard deviation (SD) of 12.4° of passive wrist extension in a group with hemiplegic CP. Rameckers et al. [26] included a more homogeneous group of children than we intend and, therefore, in the absence of clear evidence in the literature, the variability has been estimated to approximate 22° (10° greater than Rameckers et al.’s more homogenous group). Based on a SD of 22° for the primary outcome, 77 participants per group would be required to detect a 10° between-group difference in passive range of movement at 36 months with 80 % power and a two-tailed level of significance of 0.05. A 10° difference was chosen as differences greater than 5 to 10° of movement are deemed clinically important [21]. We used data from our previous successfully completed RCTs of upper limb interventions for children with CP to estimate withdrawal and loss-to-follow-up rates. Prior withdrawal rates ranged from 0 to 10 %, with an additional loss-to-follow up in these RCTs ranging from 0 to 3 % over periods of 6 months. We anticipate that loss-to-follow up in this 3 year study will be higher than 3 %, and thus estimate a 10 % loss. Consequently we predict a combined withdrawal/loss-to-follow-up rate of 20 %. Based on these estimates, we aim to recruit 194 children. Of note, children may have both limbs included in the study. The presence of two limbs was not included in the sample estimates but will be used in the analyses. Including both limbs will increase study power; hence the sample size is expected to be conservative if two limbs are included for some children. Randomised trial experience in Australia suggests we will require at least 12 months to recruit the required sample.

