### Randomisation

Once consent and assent (for those children aged 12 years or more) has been obtained by the research assistant, and following baseline assessment, children will be randomised to either the treatment or comparison group with an allocation ratio of 1:1, using a web-based randomisation procedure to ensure concealed allocation. Randomisation will be completed using randomly permuted blocks of variable length, stratified by study centre (5 strata), and by passive wrist range of movement (3 strata: wrist extension >0° (fingers extended); wrist extension between −45°-0° (fingers extended); or wrist extension < -45° (with or without finger extension)). For children with bilateral involvement, where both limbs meet inclusion criteria, both limbs will be allocated to the same intervention based on the randomisation sequence and stratification will be based on the passive wrist range of the more involved limb. Data will be collected for both upper limbs and included in the analysis at the end of the study for limb-based outcomes.

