### Statistical methods

The primary analysis will be by intention to treat. Comparison between the intervention and the control groups in the difference from baseline in the passive range of wrist extension (primary outcome) will be presented as the mean difference between the groups and its 95 % confidence interval, obtained using linear regression adjusted for the stratification factors of site and range of passive wrist extension at baseline. The regression model will be fitted using generalised estimating equations (GEE) to allow for the clustering of observations within children for those with both limbs in the study. To explore the effect of the adherence to WHO wearing schedule (i.e. a dose response relationship), a linear regression model will be fitted with compliance to treatment as a predictor and difference in the passive range of wrist extension from baseline to 36 months as the outcome, applied to all study participants. Again this model will be fitted using GEEs to allow for the clustering of limbs within participants. Evidence for an interaction between age and treatment, and between severity (Neurological Hand Deformity Classification) and treatment, will be explored by the inclusion of interaction terms in the linear regression models as well as GEE models. The analyses will be repeated, adjusting for potential confounders including occasions of upper limb BoNT-A injections and frequency of upper limb intervention. Analysis will also be undertaken using the ‘per protocol’ population excluding children who received surgical intervention or casting during the study. All data available from children who are withdrawn from the study prior to study completion will be used for analysis. Imputation of missing data will only be considered in the primary analysis if less than 10–20 % of the primary outcome is missing and will be undertaken throughout multiple imputation models.

Depending on whether data are continuous, categorical or dichotomous, the appropriate generalized linear model will be used to estimate the effect of treatment across the study period on secondary outcomes, again fitted using generalised estimating equations. All analyses will be adjusted for the same stratification factors as for the primary analysis and carried out on intention to treat and per protocol populations.

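### The primary change-score model adjusts for a three-band, worse-limb stratum rather than each limb's measured baseline, which gives up some precision, and the 80% power was calculated for a different variable

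*Protocol article*

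**What the plan says.** All references are to the Protocol article.

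- **Statistical methods.** The groups are compared "in the difference from baseline in the passive range of wrist extension (primary outcome"), and the mean difference is "obtained using linear regression adjusted for the stratification factors of site and range of passive wrist extension at baseline". The model is fitted by GEE, with limbs clustered within child. The same stratification adjustment is carried to all other analyses.
- **Randomisation.** The wrist-range factor has three levels: above 0°, −45° to 0°, and below −45°. The lowest level may be judged with or without finger extension. When both limbs qualify, "stratification will be based on the passive wrist range of the more involved limb", yet both limbs contribute data.
- **Outcome measures.** Wrist range runs from −70° to +80°, so the top band alone can span 80°.
- **Sample size.** The sizing variable is "passive range of movement of wrist extension (measured with fingers extended) at 3 years". The source study "reported a baseline standard deviation (SD) of 12.4° of passive wrist extension in a group with hemiplegic CP"; because a more mixed sample is expected, "the variability has been estimated to approximate 22"°. Then: "Based on a SD of 22° for the primary outcome, 77 participants per group would be required" to detect 10° with 80% power at two-sided 0.05. Allowing for 20% loss gives 194 children. No SD of change and no correlation between baseline and 36 months is given.

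**The concern.** Subtracting the baseline amounts to assuming that a limb's 36-month value rises one degree for every degree of baseline. If the correlation is below 1 and the two SDs are equal, the true slope is smaller. The change score then over-corrects and stays negatively related to baseline. Adjusting for the baseline in degrees removes that residual relation completely. Adjusting for three wide bands removes only the between-band part. In a child with two study limbs, the less involved limb also receives a band that describes the other limb. Precision on the primary comparison is lost although the measurement needed to recover it is already in the dataset.

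The power statement also refers to a different quantity. It uses a cross-sectional SD for the value at 36 months, whereas the analysed variable is change, whose SD depends on a correlation that the protocol does not state.

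**Working it through.** **1. Reproduce the plan's figure.** Inputs from the Sample size section: difference 10°, SD 22°, two-sided 0.05, power 80%.

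n per arm = 2 × (1.960 + 0.842)² × 22² / 10² ≈ 76.0 by the normal approximation. The t distribution gives 77, with power 80.0%. Allowing for 20% loss, 77 / 0.8 = 96.25, so 97 per arm and 194 in total. The plan's numbers reproduce, as an unadjusted comparison of 36-month values.

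**2. Residual SD under three models.** Assumptions not in the documents: SD 22° at both times, normal baseline, one limb per child, correlation r. Let v be the share of baseline variance that lies within the bands.

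- Unadjusted change: 22 × √(2(1 − r)). This equals 22° only at r = 0.5.
- Continuous baseline as covariate: 22 × √(1 − r²).
- Change adjusted for bands: 22 × √((1 − r²) + v(1 − r)²).

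The variance of the banded model relative to the continuous-baseline model is 1 + v(1 − r)/(1 + r).

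**3. Value of v.** With cut-points −45° and 0° and SD 22°, v is 0.27 at an assumed baseline mean of −20°, 0.31 at 0°, 0.53 at +20° and 0.68 at +30°. A high mean puts most limbs in the single top band, so the bands explain less.

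**4. Results at 77 per arm and a true difference of 10°** (normal approximation; ranges cover baseline means −20° to +30°).

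| r | Variance ratio, banded / continuous | Power, unadjusted change | Power, change with bands | Power, continuous baseline |
|---|---|---|---|---|
| 0.3 | 1.14–1.37 | 66% | 72–79% | 84% |
| 0.5 | 1.09–1.23 | 80.5% | 84–88% | 90% |
| 0.7 | 1.05–1.12 | 95% | 96–97% | 98% |
| 0.9 | 1.01–1.04 | about 100% | about 100% | about 100% |

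Worked example, r = 0.3 and v = 0.68: ratio = 1 + 0.68 × 0.7 / 1.3 = 1.37.

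**5. Where the banded model reaches the planned power.** Its residual SD equals 22° when v(1 − r)² = r², that is r = √v / (1 + √v). For v = 0.27 this is 0.34; for v = 0.68 it is 0.45. The normal approximation puts the limits slightly lower, hence roughly 0.3 to 0.45.

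**6. Children with two limbs.** A limb-level simulation used 1,500 trials per setting, baseline mean 20°, 40% of children bilateral, between-limb correlation 0.6, the stratum from the worse limb and cluster-robust standard errors. The bilateral share and the limb correlation are assumptions.

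| r | SE, bands | SE, continuous | Variance ratio | Power, bands vs continuous |
|---|---|---|---|---|
| 0.3 | 3.71 | 3.29 | (3.71/3.29)² = 1.27 | 76.5% vs 85.7% |
| 0.5 | 3.20 | 2.91 | 1.21 | 86% vs 91% |
| 0.7 | 2.56 | 2.44 | 1.10 | 97% vs 98% |
| 0.9 | 1.55 | 1.52 | 1.04 | about 100% for both |

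**The case against.** **The covariate may already be the measured range.** The Statistical methods text names baseline wrist extension without saying that it is banded, and a condensed article may leave the coding to the analysis plan. If degrees are meant, the precision point disappears. But the text calls it a stratification factor, and the only definition of that factor is the three bands. The banded reading is the natural one, and the alternative would need the same clarifying sentence.

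**The analysis is valid.** Adjusting a change score for the randomisation factors is unbiased under randomisation and is common practice. This stands. A reader might infer that the baseline is ignored or that the change score is itself an error. Neither follows: the baseline is subtracted, and once a limb's continuous baseline is in the linear model, change and 36-month outcomes give the same treatment estimate.

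**The power mismatch may be harmless.** Under randomisation the expected group difference is the same for change and for the 36-month value, so the 10° target serves both and only the SD differs. The protocol also calls its size conservative because second limbs were not counted. Both remarks are fair.

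**Low r may be pessimistic.** At r = 0.3 the SD of change is 26.0°. Even with no average loss, about 12% of limbs (30 / 26.0 = 1.15 SD) would lose 30° or more, the amount that the protocol treats as grounds for closer monitoring. That is indirect, but it cautions against resting the case on the r = 0.3 row.

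**The worse-limb mismatch is narrow.** It affects only children with two study limbs, and their share is not given.

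**Age.** The Background says that "increasing stiffness and progressive loss of range of movement occurs throughout childhood and adolescence", so a reader might want age in the model too. No gain from it has been quantified, and measured baseline may already carry much of that information. It is not part of this point.

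**Conclusion.** The point holds as one of efficiency and consistency, not validity. As written, the primary model uses a coarse, child-level version of a covariate that is measured in degrees on every limb. The cost is 14 to 37% extra variance at r = 0.3, 9 to 23% at 0.5, 5 to 12% at 0.7 and 1 to 4% at 0.9. These figures assume equal SDs of 22°, a normal baseline with mean between −20° and +30°, and one limb per child; the two-limb simulation falls in the same range.

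The 80% power is correctly calculated, but for an unadjusted comparison at 36 months. A reader might conclude that the trial is underpowered. The document does not support that: r is not stated, and the banded model falls short of 80% only when r is below roughly 0.3 to 0.45. What can be said is that the planned power is not guaranteed for the stated model. With continuous baseline adjustment it would be a lower bound, because 22 × √(1 − r²) cannot exceed 22°. That protection covers uncertainty about r only. If the 36-month SD is larger than 22°, a figure the protocol itself presents as an estimate, no choice of covariate restores the stated power.

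**What to change.** In Statistical methods, add each limb's own measured baseline passive wrist extension (fingers extended, in degrees, continuous) as a covariate in the primary GEE model, and keep site and the randomisation stratum. The outcome can stay as change, since the treatment estimate is then the same as for the 36-month value. State that the stratum is the child-level band used at randomisation.

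In Sample size, say that 80% power at SD 22° refers to an unadjusted comparison of 36-month values, and that it is a lower bound under continuous baseline adjustment if that SD holds.

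The cost is one or two sentences and one extra model parameter. No new data are needed. The change should be made before unblinded outcome data are seen.

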#### Intervention – modifications

Children in either group could lose range of movement through the trial period as this is the natural history of CP. In addition, the trial will run for an extended period (3 years) during which growth and physical development will influence children’s outcomes. Both groups will, therefore, be carefully monitored for loss of range of motion over time.

Children will be monitored for the first 12 months following enrolment according to the study protocol and will not receive any modification to the intervention during this period. Children assessed at or after the 12-month time point who have lost ≥30° passive range of wrist extension or increased by ≥2 categories on the Modified Ashworth Scale, compared to baseline, in either group will be eligible for increased monitoring. This involves reassessment at 3-monthly intervals and may, in consultation with the child’s parents and treating team, involve either serial casting to regain range of movement and/or a referral for a surgical opinion. Casting is common clinical practice in children with CP to achieve increased passive range of motion over the short term [10].

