### Outcome measures

The primary outcome measure is passive range of wrist extension (measured with the fingers extended). Range of wrist movement is operationalised from -70° (full wrist flexion) to + 80° (full wrist extension) where 0° indicates a neutral position. Range of movement will be measured using a goniometer for extension/flexion movements, an inclinometer for supination/pronation and inertial motion sensors. Inertial motion sensors, constructed specifically for the trial, will be used to measure active and passive wrist extension, with fingers extended as well as functional range of wrist extension elicited during standardised tasks. Other measures across the domains of the ICF will also be used to evaluate the effect of the intervention. Table 2 displays each variable, the measurement tool selected and provides an overview of psychometric evidence for the selected tools.

**Table 2 Tab2:** Variables and outcome measures

Variable	Measurement tool	Additional information
ICF level: Body function: baseline, 6, 12, 18, 24, 30, 36 months		
Passive range of motion: elbow extension, wrist extension (with fingers extended), wrist extension (with fingers flexed), supination	Standardised goniometric measurement; inclinometer for measures of supination;	Goniometric measurements have a high level of intra-rater reliability when measuring passive range of movement in the lower limb in children with CP (ICC >.80) and SEM of 3.5° [44, 45].
	Inertial Motion sensors.	Inertial motion sensors (see additional information below) will be used to measure passive wrist extension with fingers extended only.
Active range of movement: elbow extension, wrist extension (with fingers extended), wrist extension (with fingers flexed), supination	Standardised goniometric measurement and use of inclinometer for measures of supination.	See additional information above.
	Inertial Motion sensors	Inertial motion sensors (see additional information below) will be used to measure active wrist extension with fingers extended only.

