### Data collection methods for child-participants who exit prematurely

Children may exit prematurely from the study because of voluntary withdrawal or termination of WHO intervention due to harm (e.g. allergic reaction to materials). Participant retention will be supported within the study through provision of routine follow-up and regular feedback on child progress via the TherApp summary report that can be generated by parents throughout the trial. Where possible, all children will be followed to the study end point (3 years) so that data are available for analyses. Lack of adherence to the treatment plan will be recorded using TherApp and will not constitute a reason for withdrawal. Reasons for withdrawal from the intervention, or the study, will be recorded to assist with management of missing data and interpretation of results.

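### The per-protocol set excludes children who had casting or surgery, which the protocol allows in response to loss of the primary outcome, so the supporting analyses select on outcome

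*Protocol article*

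**What the plan says.** Statistical methods makes intention to treat the primary analysis and then adds an analysis in a per-protocol "population excluding children who received surgical intervention or casting during the study". No other criterion for that population is given. The section ends by extending both populations to all analyses, so the exclusion reaches the primary and every secondary outcome.

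Intervention – modifications says when casting or surgery may enter. At or after 12 months, children who have "lost ≥30° passive range of wrist extension or increased by ≥2 categories on the Modified Ashworth Scale, compared to baseline, in either group" become eligible for closer monitoring. After consultation with parents and the treating team, this may "involve either serial casting to regain range of movement and/or a referral for a surgical opinion".

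Outcome measures states: "The primary outcome measure is passive range of wrist extension (measured with the fingers extended"). The Modified Ashworth Scale is listed there as the measure of muscle stiffness, a secondary outcome.

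Two other sections matter. Criteria for withdrawal lets children with surgery, or with more than three casting episodes, stop study treatment, but follows them to the end and analyses them where possible. On adherence, the section on premature exit says: "Lack of adherence to the treatment plan will be recorded using TherApp and will not constitute a reason for withdrawal".

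**The concern.** A per-protocol set is meant to hold children who were treated as the protocol intended. This one is defined by an event after randomisation that the protocol itself permits and links to deterioration in the primary outcome. A child cast once, after a triggering assessment, has followed the protocol and is still on study treatment under the withdrawal criteria, yet is excluded.

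Two distortions follow. If the orthosis prevents large losses of range, more controls than orthosis children reach the trigger, more poor-outcome controls are removed, and the per-protocol difference shrinks. If the orthosis does nothing, a difference can still appear should casting be chosen more readily in one arm. Casting is decided with families, who cannot be blinded. The section on assessors and blinding accepts that unblinded therapists may adjust co-interventions differently by group.

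The trial would then report a planned second result that dilutes, or seems to contradict, the intention-to-treat result on its main question.

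**Working it through.** **The passages side by side**

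| Event | Status elsewhere in the protocol | Status in the per-protocol set |
|---|---|---|
| One to three castings after a triggering loss | Authorised modification; study treatment continues | Excluded |
| Surgery, or more than three castings | May stop study treatment; followed and analysed where possible | Excluded |
| Orthosis not worn as asked | Recorded; no reason for withdrawal | No rule stated |

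**The plan's own figure.** The protocol gives no number for this point. The SD and the difference used below come from its sample-size section, which reproduces. A two-sample t-test calculation with a 10° difference, SD 22°, two-sided 5% and 80% power gives 76.95, so 77 per group. Then 77/0.8 = 96.25, so 97 per group and 194 in all.

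**Illustration of the selection.** Assumptions not in the documents:
- change from baseline is normal, with SD 22° used for change;
- mean change is −10° in controls and 0° with the orthosis;
- the 30° trigger acts on the final change;
- a fraction q of triggered children is cast or operated on, and so excluded.

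With a = (−30 − μ)/SD, p = Φ(a) and φ the normal density, the mean among children kept is

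μ + q·SD·φ(a)/(1 − q·p).

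- Control: a = −20/22 = −0.909, p = 0.182, φ = 0.2639, SD·φ = 5.806.
- Orthosis: a = −30/22 = −1.364, p = 0.086, φ = 0.1574, SD·φ = 3.464.

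| q | Control mean kept | Orthosis mean kept | Difference (true 10°) |
|---|---|---|---|
| 1 | −10 + 5.806/0.818 = −2.9 | 3.464/0.914 = 3.8 | 6.7° |
| 0.5 | −10 + 2.903/0.909 = −6.8 | 1.732/0.957 = 1.8 | 8.6° |
| 0.25 | −10 + 1.451/0.955 = −8.5 | 0.866/0.978 = 0.9 | 9.4° |

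**Range.** With control decline of 5° to 20° and SD from 12.4° (the cited baseline SD) to 22°, the difference is 5.4° to 9.4° for q = 1, 8.5° to 9.7° for q = 0.5, and 9.3° to 9.9° for q = 0.25.

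**Trigger at an earlier visit.** Suppose two-thirds of the mean change has occurred by then, with SD 22° and correlation r with the final change. The added term is multiplied by r, and a uses the earlier mean. For r = 0.5 to 0.7, the difference is 9.0° to 8.6° if all triggered children are excluded and 9.6° to 9.4° if half are.

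**No true effect.** Take mean −10° in both arms. If 75% of triggered controls but 25% of triggered orthosis children are excluded, the means kept are −10 + 0.75 × 5.806/0.864 = −5.0 and −8.5. That is a false 3.5° in favour of control; reversing the split reverses the sign. The split is invented to show the mechanism, and nothing in the documents supports those percentages.

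**The case against.** The strongest reply is that nothing here touches the main result. Intention to treat is primary, and children with casting or surgery are followed and analysed where possible. That is correct, and it makes this a point about supporting analyses.

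A reader might infer that the rule deletes the worst outcomes outright. The documents do not support that:
- The trigger opens closer monitoring. Casting or referral is discretionary, and a referral for an opinion is not surgery.
- Loss is judged from 12 months onward, not at 36 months, and casting aims to regain range, so a cast child need not be among the lowest at the end.
- The Ashworth trigger is separate from range and is not in the illustration.
- Surgery or casting may also arise outside this pathway.

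So 6.7° is close to a worst case under its assumptions, and the partial-casting figures belong beside it.

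A reader might also infer that non-adherent children are knowingly retained. The article states no adherence rule for the set, but that is partly silence, which an analysis plan not shown here could fill. Adherence is not ignored either: daily wear is collected, and a dose-response model is planned in all participants. What stands is narrower. The exclusion that is stated depends on outcome, and adding adherence criteria to it would not remove that dependence.

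**Conclusion.** The concern holds as a should-fix on a supporting analysis. The stated exclusion conditions on a post-randomisation event tied to the primary outcome and to a secondary outcome, and it removes children who were managed as the protocol allows. If the orthosis works, the exclusion tends to pull the contrast toward no effect. If casting decisions differ by arm, bias can go either way.

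The possibility of selection follows from the rule; its size cannot be derived from the documents. Under the stated assumptions, attenuation of a true 10° ranges from about 0.6° (a quarter of triggered children excluded) to 3.3° (all excluded), and is smaller if the trigger is an earlier measurement. For scale, the sample-size section treats differences above 5° to 10° as clinically important.

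**What to change.** 1. Remove casting and surgery as per-protocol exclusions.
2. If a per-protocol set is kept, define it by adherence to allocation, using the wear data already collected. Label it supportive, and say that it too is selected after randomisation, since pain or difficulty with wear may relate to outcome.
3. Address casting and surgery in a supplementary analysis of the 36-month outcome that keeps every randomised child. Use the 6-monthly measurements up to the first casting or surgery, and treat later values as missing in a likelihood-based repeated-measures model or by multiple imputation. This is preferable to carrying the last earlier value forward, which would mix 12- to 30-month values with 36-month values.

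The cost is revised wording and one extra analysis, with no new data. The supplementary analysis relies on a missing-at-random assumption. That is easier to defend when a recorded assessment led to the casting than when surgery arose through usual care, and the report should say so.

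### Imputation of the primary outcome is allowed only below a cut-off given as a range, and is off at the 20% loss for which the trial is sized

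*Protocol article*

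**What the plan says.** All places are in the protocol article.

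- **Statistical methods, imputation:** "Imputation of missing data will only be considered in the primary analysis if less than 10–20 % of the primary outcome is missing". The method named is multiple imputation. No alternative is named for higher missingness.
- **Statistical methods, sentence just before:** "All data available from children who are withdrawn from the study prior to study completion will be used for analysis".
- **Statistical methods, primary model:** a linear regression of the difference from baseline in passive wrist extension, adjusted for site and baseline range. It is fitted by GEE, and the only reason given for the GEE is that some children contribute two limbs. Repeated visits are not mentioned. For secondary outcomes, by contrast, the effect is estimated over the whole study period.
- **Sample size:** "77 participants per group would be required to detect a 10° between-group difference in passive range of movement at 36 months", then "Consequently we predict a combined withdrawal/loss-to-follow-up rate of 20" per cent, then "Based on these estimates, we aim to recruit 194 children".
- **Outcome measures, Table 2:** the schedule for the domain that contains passive wrist extension is "ICF level: Body function: baseline, 6, 12, 18, 24, 30, 36 months".
- **Data collection methods for child-participants who exit prematurely:** children are to be followed to 3 years where possible, and poor adherence is not grounds for withdrawal.

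**The concern.** The rule is explicit, so this is not detail left to a later document. It has three weaknesses.

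1. A cut-off of 10–20% does not settle what happens between those values, and imputation is only to be considered even below it. How missing primary outcomes are handled could therefore be decided after results are known.
2. It allows imputation when little is missing and withholds it when much is missing, which is when the assumption about dropout matters most.
3. It excludes the loss rate that the plan itself forecasts.

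Once imputation is off, nothing stated brings a child without a 36-month value into the primary comparison, even if that child has several interim measurements of the same variable. At stake are the precision of the 36-month difference and, if dropout depends on earlier loss of range, its freedom from bias.

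**Working it through.** **1. The plan's own figure.** Inputs from Sample size: difference 10°, "Based on a SD of 22° for the primary outcome", "80 % power and a two-tailed level of significance of 0.05". The normal approximation gives 76 per group. The noncentral t calculation gives power 0.795 at 76 and 0.800 at 77, so 77 reproduces. Inflation for 20% loss: 77 / 0.8 = 96.25, rounded up to 97 per arm; 2 × 97 = 194. The sample size is sound. It treats 0.20 × 194 = 38.8, about 39 children, as having no 36-month outcome.

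**2. The rule at the predicted rate.** 20% is not less than 20%, and not less than 10%. Imputation is off at either end of the range.

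**3. How often each cut-off is reached.** Take the number missing as binomial with n = 194. Missingness of at least 10% means 20 or more children (10% is 19.4); at least 20% means 39 or more (20% is 38.8). The last column is the difference of the two before it.

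| True rate | P(observed ≥10%) | P(observed ≥20%) | P(between: rule undetermined) |
|---|---|---|---|
| 10% | 0.478 | <0.001 | 0.48 |
| 15% | 0.978 | 0.033 | 0.94 |
| 20% | 0.9999 | 0.514 | 0.49 |
| 25% | >0.9999 | 0.954 | 0.05 |

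At the predicted 20%, imputation is barred on any reading about half the time. Almost all of the remainder falls where the text does not decide.

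**4. What remains when imputation is off.** The outcome is change from baseline to 36 months and the stated clustering is limbs within child. A child with no 36-month value has no outcome in that regression. Measurements at 6, 12, 18, 24 and 30 months exist but have no stated role in the primary model.

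**5. Illustrative size.** The documents give no dropout mechanism or correlation between visits, so these inputs are assumptions: 97 per arm, one limb per child, SD 22°, control loss of 10° over 36 months, true effect 10°, correlation between baseline and 36 months of 0.5 or 0.7, 400 runs per case. Dropout is logistic in the loss of range at the previous visit. The analysis is a baseline-adjusted regression at 36 months. Imputation here is by regression on baseline and interim values within arm (a single conditional mean, enough to show the point estimate).

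| Dropout assumed | Missing | Completers only | Using interim visits |
|---|---|---|---|
| Random | 20% | 10.2° and 9.8° | 10.3° and 9.9° |
| Depends on loss, equally in both arms | 15–17% | 9.4° and 9.6° | 10.0° and 10.0° |
| Depends on loss, control arm only | 22–24% | 5.3° and 7.1° | 9.8° and 10.1° |

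Each pair is for correlation 0.5 and 0.7. Under random dropout the two approaches differ only in precision: the empirical standard error was 3.22° and 2.54° for completers against 3.13° and 2.40° with the interim visits. A separate simulation (1,500 runs, random slopes SD 18°, error SD 7°, dropout odds rising with observed loss, 15–18% missing) gave 9.1–9.2° for completers and 10.1° using the interim visits.

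**The case against.** The strongest reply is that the protocol nowhere prescribes a completers-only analysis and says that data from withdrawn children will be used. That is correct. A reader might infer that the plan orders a complete-case analysis and so contradicts itself. The text does not go that far: completers-only is what the stated model implies when nothing is imputed, and the sentence on available data is unreconciled with the model because no mechanism connects them.

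Second, the 20% is a combined withdrawal and loss rate, not a forecast of missing 36-month values. Children who exit are followed where possible, so actual missingness may be lower. This stands, but the sample size still budgets for the full 20%, and a lower rate such as 15% would usually fall in the undetermined band.

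Third, the milder simulated biases arise at 15–18% missing, where the upper reading would still allow imputation. They are also small: 0.4–0.9° against a planning standard error of 22 × √(2/77) = 3.5°, at most about a quarter of one standard error. The large biases need dropout driven by lost range in controls only, which no section supports. All of this stands.

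Fourth, a reader might infer that bias would run towards no effect because deteriorating controls leave. The documents do not show this. The reasons for exit that they name include harm from the orthosis, and the Background mentions discomfort and carer burden, which point at least as much to the orthosis arm. Under Criteria for withdrawal, children who have surgery or repeated casting are to be followed to the end. Nor is intention to treat broken: children are analysed as randomised, and the open question is how missing outcomes are handled.

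Finally, multiple imputation can be thought unreliable when much is missing. Dropping the affected children is not safer, because it discards their interim values and relies on a stronger assumption about dropout.

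**Conclusion.** The point holds as a badly fixed rule that should be changed. Three things rest on the text alone: the cut-off is a range, it withholds imputation when missingness is greatest, and it excludes the 20% loss used to reach 194. It also rests on the text that the primary model states no use of the five interim visits. The probability of about one half at the 20% cut-off, and near certainty at the 10% cut-off, assumes that 20% is the true missing rate and that children drop out independently.

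Bias is a possibility, not a demonstrated result. Its direction and size depend on a mechanism that the documents do not give: none if dropout is unrelated to range, about 0.4–0.9° on 10° in the milder cases simulated, and about 3–5° if dropout follows lost range in one arm only. The sample size is not in error.

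**What to change.** Delete the percentage threshold and state one primary approach that applies whatever proportion is missing and uses every scheduled passive-range measurement. Either of these would do:

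- multiply impute the 36-month value, separately by arm, from baseline and the 6–30 month values, and then fit the planned GEE; or
- fit a repeated-measures model to all visits, with limbs nested within child and the planned adjustments, and take the 36-month contrast as primary.

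Keep the completers-only GEE as a sensitivity analysis. Reword the sentence on available data from withdrawn children so that it names the chosen mechanism.

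The cost is a change of wording and a little more programming. No additional children, visits or measurements are needed, and the target of 194 stands.
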